### Sample size

An a priori sample size calculation was conducted using the eta-partial square value of the group-by-time interaction for worst knee pain (0.19) obtained in a previous study that compared the effects of three gait retraining programs on runners with patellofemoral pain [27]. In G*Power software [28], we used ANOVA: repeated measures, within-between interaction, with the following parameters: effect size f = 0.48 (obtained through eta-partial square value); level of confidence = 0.05; power = 99%; number of groups = 3; number of measurements = 3. The total sample size obtained was 21 participants, however, to account for losses during the follow-up period, the final sample size will be 30 participants.

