### Outcomes measures (dependent variables)

The primary outcome of the study will be: (I) pain during daily activities (usual)—assessed using the Visual Analog Pain Scale [29]; The secondary outcomes will be: (II) pain during running—assessed using the Visual Analog Pain Scale [29]; (III) function—assessed using the Patellofemoral Disorders Scale [31]; (IV) kinematics of the lower limbs in the frontal (contralateral pelvic drop; hip adduction) [33,35,36] and sagittal planes (foot inclination; tibia inclination; ankle dorsiflexion; knee flexion) [33,37,38]–assessed through digital videos using two webcams (MyoVideo 139 HD Color Webcam) sampling at 30 frames per second and two leds (LED Floodlight) [33]. The video recordings will be analyzed using the MyoResearch 3.14 –MyoVideo software (Noraxon U.S.A. Inc.). The kinematic variables of interest were chosen based on previous studies [14,15,19,47,48]. The systematic review and meta-analysis of Neal and colleagues [14] shows a relationship between increased hip adduction and contralateral pelvic drop with PFP. The study of Wille and colleagues [47] showed that foot inclination angle and peak of knee flexion are variables that may predict knee joint loading and PFJ forces during running. Tibia inclination during initial contact is related with cadence and length [48] and these are associated with PFJ forces [18,19]. For the comparison of the three study subgroups, the average of points on the visual analog scale of pain, average of points on the scale of Patellofemoral disorders and the peak in degrees of the contralateral pelvic drop, hip adduction, knee flexion and ankle dorsiflexion during midstance and foot inclination and tibia inclination during the initial contact will be considered. The three groups will be compared before (t0), immediately after (t2) and six months (t24) after starting the protocol.

Regarding the retention of the participants, to ensure that there are minimal losses during the follow-up period, the researchers will make a monthly phone call to monitor pain, the current level of training, physical activity practice and if the participants sought for other methods of treatment. Participants can withdraw from the study for any reason at any time, in which case the researchers will collect the pain and function outcomes using the aforementioned instruments (if possible) and report the reasons why these patients did not complete the follow-up (Fig 1).

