### Data analysis

The data of each participant will be extracted for SPSS (Statistical Package for Social Sciences) version 23.0 for later statistical analysis. Descriptive analysis will be performed with calculation of means, standard deviations and 95% confidence intervals for quantitative variables and frequencies and percentages for qualitative variables. Data normality and sphericity will be tested using the Shapiro-Wilk and Mauchly’s tests, respectively. Baseline demographic data will be compared using ANOVA (parametric data), Kruskall-Wallis (non-parametric data) and Chi-squared tests. To compare the effects of the rehabilitation programs on the outcomes of the study, a repeated measures ANOVA with a 3-by-3 mixed-model (parametric data) or the Generalized Estimation Equations procedure with gamma distribution model (non-parametric data) will be used. Time (t0 x t2 x t24) will be used as repeated factor, group (impact x cadence x control) as independent factor and the mean of points on the visual analog pain scale, mean of points on the Patellofemoral Disorders Scale, and the peak in degrees of the contralateral pelvic drop, hip adduction, ankle dorsiflexion and knee flexion during midstance, and foot inclination and tibia inclination during initial contact as dependent variables. Baseline characteristics that are different across groups will be included as covariates in the model. Significance level of p <0.05 will be adopted. Sidak’s post-hoc will be used to make pairwise comparisons. Subgroup analysis and adjusted analysis will not be performed. Intention-to-treat analyses will be conducted where the subjects will be analyzed independently of adherence to the protocol or retention in the follow-up.

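### The rules for participants who withdraw or drop out injured are not tied to t2 or t24 and leave out kinematics, which does not fit an analysis of all subjects at three fixed times

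*Protocol article*

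**What the plan says.** The protocol article deals with people who leave in two places.

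- **Outcomes measures (dependent variables).** Participants may withdraw at any time, "in which case the researchers will collect the pain and function outcomes using the aforementioned instruments (if possible". The reasons for not completing follow-up are also to be reported. No assessment date is attached. Kinematics, listed as an outcome in the same section, is not mentioned.
- **Rehabilitation programs (independent variables), closing paragraphs.** A participant whose pain makes continuing impossible counts as a drop-out from the intervention because of injury. The data gathered up to then go into the analysis. No later collection is mentioned.

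Two other statements fix what the analysis needs. On timing: "The three groups will be compared before (t0), immediately after (t2) and six months (t24) after starting the protocol". On the population, under Data analysis: "Intention-to-treat analyses will be conducted where the subjects will be analyzed independently of adherence to the protocol or retention in the follow-up". The same model, with time at t0, t2 and t24, is to be applied to pain, function and all six angles.

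Under Sample size, "The total sample size obtained was 21 participants", and "to account for losses during the follow-up period, the final sample size will be 30 participants". No loss rate is given. Monthly telephone calls that ask about pain are planned for everyone, but as a retention measure and not as outcome assessments.

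**The concern.** The secondary objective is the effect at six months, and the hypothesis is that benefit lasts that long. Both depend on t24 scores. A pain score taken at week 10 because a runner left then has no level in a model whose times are t0, t2 and t24. It is either set aside or treated as something it is not.

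If it is set aside, the t24 comparison describes mainly those who stayed. The protocol itself foresees that pain can cause drop-out, so leaving may be related to outcome. It may also differ by arm, because the control group has no retraining to drop out of. If the score is relabelled t24, early benefit is carried into the six-month result, in the direction of the hypothesis whenever benefit fades.

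For the angles, the protocol names no route to a value after withdrawal. Those results describe people still attending and able to run at 10–12 km/h, while the intention-to-treat sentence makes no exception for them.

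This is about which data are collected and when. A later analysis document can decide how to handle gaps, but it cannot supply t2 or t24 scores that nobody asked for.

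**Working it through.** **1. The rules against the model**

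| Participant | Pain and function | Kinematics | What the model needs |
|---|---|---|---|
| Completes | t0, t2, t24 | t0, t2, t24 | t0, t2, t24 |
| Withdraws | if possible, no date given | not named | t0, t2, t24 |
| Injury drop-out | what was already collected | what was already collected | t0, t2, t24 |

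Someone lost after t2 keeps a valid t2 score. For that person the gap is at t24.

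**2. The plan's own sample size and its implied loss allowance**

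Inputs from Sample size: partial eta squared 0.19; "effect size f = 0.48 (obtained through eta-partial square value"; "level of confidence = 0.05; power = 99%; number of groups = 3; number of measurements = 3". The correlation between repeated measures is not stated; I assume 0.5, with sphericity.

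- f = √(0.19/0.81) = 0.484, which agrees with 0.48.
- Noncentrality = f² × N × 3/(1 − ρ) = 0.2304 × 21 × 3/0.5 = 29.0, with df = 4 and 36. Power is 99.04%, so 21 is reproduced.
- With all 30, power is 99.97%.
- Implied allowance: (30 − 21)/30 = 9/30 = 30%.

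The power with 21 depends on the assumed correlation: 82.8% at ρ = 0, 94.5% at ρ = 0.3 and 99.0% at ρ = 0.5. These figures concern the overall interaction test and take the planning inputs as given. On those inputs, with ρ = 0.5, losing 9 people is not a power problem. The issue is bias and what the t24 result describes.

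**3. Size of the bias if withdrawal scores were entered as t24**

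Assumptions, none of them from the protocol: the between-arm benefit is e at week 2 and falls linearly to 0 at week 24; a fraction w of each arm withdraws, spread evenly over that interval; each withdrawal score is entered as t24. The average benefit at withdrawal is then e/2, and the apparent t24 difference is w × e/2, where the truth is 0.

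| w | e (VAS points) | False t24 benefit |
|---|---|---|
| 10% | 2 | 0.10 × 2/2 = 0.10 |
| 30% | 2 | 0.30 × 2/2 = 0.30 |
| 30% | 3 | 0.30 × 3/2 = 0.45 |

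For scale, the standard error of a two-arm difference with 10 per arm is SD × √(2/10) = 0.447 × SD. With an assumed SD of 2 it is 0.89. The three values are then 0.11, 0.34 and 0.50 of a standard error. A larger SD makes these ratios smaller, and a smaller SD makes them larger.

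If withdrawal scores are not used, or if benefit does not fade, this particular bias is zero. In the first case the t24 values are still missing.

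**The case against.** The strongest reply is that much of this is inferred. The withdrawal sentence does not say that scores are taken at the moment of leaving. The words about timing describe when a person may withdraw, and the questionnaires might still be sought on schedule. The flow diagram is not available to settle it, and a condensed article may omit a date that the full protocol gives. This stands in part. A reader might infer that scores are taken at withdrawal and not at t2 or t24; that is the natural reading, but the text neither states it nor rules it out. The missing date is the defect.

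Other tempting readings also go too far:

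- A reader might infer that up to 30% will have no valid six-month score. The 30% is only the allowance implied by raising 21 to 30. Actual loss could be lower or higher, and some of it would be people who cannot be reached under any rule.
- A reader might infer that every outcome is promised regardless of retention. The Data analysis section promises that subjects will be analysed, not that every outcome will be collected.
- A reader might infer that early values are to be carried forward. Nothing in the protocol says so, and the bias figures depend entirely on that step.
- The lack of a missing-data method is not a finding, since it is commonly left to the analysis plan. The generalized estimating equations option can use t0 and t2 from someone lost later.

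It is also fair that a laboratory treadmill run often cannot be obtained from someone who has left, so missing kinematics are a practical limit more than an error. What remains is that the stated collection rules do not secure the scores that the stated analysis uses.

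**Conclusion.** The point holds as a mismatch between two collection rules and the analysis they feed. Neither rule is tied to t2 or t24, the withdrawal rule leaves out kinematics, and the analysis has only three times and covers all subjects whatever their retention. If the rules are followed as they naturally read, six-month scores of people who leave are lost for good.

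The size is uncertain and probably modest. Under the stated assumptions, a false six-month benefit of about 0.1 to 0.3 VAS points arises for a 2-point early benefit (0.45 for 3 points and 30% withdrawal), but only if off-schedule scores are relabelled t24. Otherwise the cost is missing t24 values, and a comparison resting mainly on those who stayed. The kinematic part is a minor reporting point. The change is still worthwhile because it is cheap and can only be made prospectively.

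**What to change.** - **Outcomes measures and Rehabilitation programs:** state that a participant who stops the intervention or withdraws from visits is asked, if they agree, to complete both VAS items and the Patellofemoral Disorders Scale at the scheduled t2 and t24 dates by remote contact. The monthly calls already planned can be used to arrange this. State that a score taken at withdrawal is not entered as t2 or t24. This concerns data collection only and does not touch the clinical handling of worsening pain.
- **Data analysis:** describe the kinematic results as based on participants who completed the treadmill run, and report by arm how many runs are missing and why.

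Cost: some rewording and at most two remote questionnaire contacts per person who leaves, about nine people if losses match the implied allowance. Some will refuse, so the gap will shrink but not close. The kinematic claim becomes narrower.

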**Fig 1 pone.0250965.g001:**
[figure not shown]
Diagram of the study.

### Data analysis

The data of each participant will be extracted for SPSS (Statistical Package for Social Sciences) version 23.0 for later statistical analysis. Descriptive analysis will be performed with calculation of means, standard deviations and 95% confidence intervals for quantitative variables and frequencies and percentages for qualitative variables. Data normality and sphericity will be tested using the Shapiro-Wilk and Mauchly’s tests, respectively. Baseline demographic data will be compared using ANOVA (parametric data), Kruskall-Wallis (non-parametric data) and Chi-squared tests. To compare the effects of the rehabilitation programs on the outcomes of the study, a repeated measures ANOVA with a 3-by-3 mixed-model (parametric data) or the Generalized Estimation Equations procedure with gamma distribution model (non-parametric data) will be used. Time (t0 x t2 x t24) will be used as repeated factor, group (impact x cadence x control) as independent factor and the mean of points on the visual analog pain scale, mean of points on the Patellofemoral Disorders Scale, and the peak in degrees of the contralateral pelvic drop, hip adduction, ankle dorsiflexion and knee flexion during midstance, and foot inclination and tibia inclination during initial contact as dependent variables. Baseline characteristics that are different across groups will be included as covariates in the model. Significance level of p <0.05 will be adopted. Sidak’s post-hoc will be used to make pairwise comparisons. Subgroup analysis and adjusted analysis will not be performed. Intention-to-treat analyses will be conducted where the subjects will be analyzed independently of adherence to the protocol or retention in the follow-up.

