### Participants

The eligibility criteria will be: Inclusion–(I) rearfoot striking runners with cadence under 170 steps/minute; (II) age between 18 and 45 years; (III) pain around or behind the patella, with intensity of at least 3/10 on the Visual Analogue Scale (VAS), during running and one task among squatting, climbing, and descending steps, kneeling and extending the knee with resistance [24]; (IV) being comfortable running at a speed of 10–12 km/hour. Exclusion—(I) Other disorders in the lower limbs; (II) history of surgery in the lower limbs in the last year; (III) not showing interest to adhere to a strict running retraining protocol for 2 weeks. Participants with unilateral or bilateral symptoms will be included, however, in the second case, only the worst knee (pain intensity) will be considered for analysis. The participants will be recruited through contact via e-mail, telephone, and through personnel with Goiânia’s running clubs in search of runners with PFP. In this first contact, general (gender, age, body mass, height, body mass index, history of injury and previous surgeries in the lower limbs), running (experience, volume, frequency) and pain information (intensity, location, duration of symptoms and functional tasks related to pain) will be assessed to see if the participants are eligible. Based on pain information, the diagnostic will be established using the following criteria: pain around or behind the patella during functional activities that loads the patellofemoral joint [24]. A systematic review of reviews concluded that anterior knee pain produced by functional tasks is currently the best diagnostic indicator of PFP [25]. Also, PFP is evident in 80% of the people who present anterior knee pain during a squatting manoeuvre [26].

Ethics approval was obtained from the Institutional Review Board of University of Brasilia/Faculty of Ceilândia (4.132.491), and all subjects will sign a detailed consent form before entering the study (S2–S4 Files). This study was registered in the Brazilian Registry of Clinical Trials (RBR-8yb47v) (S6 File).

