### Data collection

Pain will be assessed using the Visual Analog Pain Scale [29], which consists of a numerical scale from 0 to 10 points, where 0 means no pain and 10 means the maximum pain ever experienced. Pain during daily activities (usual) and running will be measured. VAS is a reliable and valid scale for patients with PFP [30]. Function will be assessed using the Patellofemoral Disorders Scale [31], which contains 13 questions that assess the severity of symptoms and limitations in different activities related to PFP. It presents a score between 0 to 100 points where the lower the score the worse the function. The Patellofemoral Disorders Scale is a reliable and valid scale for patients with PFP, which has been translated into Portuguese [30,31]. The kinematics of the lower limbs will be assessed through digital videos using two webcams (MyoVideo 139 HD Color Webcam) sampling at 30 frames per second and two leds (LED Floodlight) [32]. Reflective markers will be placed on the manubrium sterni and bilateral on the anterior superior iliac spine (ASIS), greater trochanter, lateral femoral epicondyle, fibular head and lateral malleolus [33]. All participants will be instructed to run at 10–12 km/hour on a motorized treadmill (Movement XL 1600). A treadmill acclimatization period of 6 min will be used before running kinematics are measured [34]. The frontal plane camera will be placed on a portable tripod perpendicular to the frontal plane at a height of 1.30m and a distance of 2.55m from the treadmill. The sagittal plane camera will be placed on a portable tripod, perpendicular to the sagittal plane at a height of 1.15m and a distance of 2.50m from the treadmill. The video recordings will be analyzed using the software MyoResearch 3.14—MyoVideo (Noraxon U.S.A. Inc.). In the frontal plane the angles assessed will be: contralateral pelvic drop; hip adduction [33,35,36]. These angles will be evaluated during midstance. In the sagittal plane the angles assessed will be: foot inclination; tibia inclination; ankle dorsiflexion; knee flexion [33,37,38]. Foot and tibia inclination will be evaluated during initial contact while ankle dorsiflexion and knee flexion during midstance. In the frontal plane, the deepest landing position (near midstance) will be determined visually by slowly advancing the video frame by frame [33,37,38]. Since the cameras are synchronized this position will also be used to determine the midstance in the sagittal plane. Initial contact will be determined visually by slowly advancing the video frame by frame, and will be defined as the first time that the foot touched the ground [37]. To analyze the proposed angles, seven steps will be considered [33]. The study of Dingenen and colleagues [39] has found excellent inter-rater reliability (ICC) for all angles with ICC’s ranging from 0.93 to 0.99.

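### A Shapiro-Wilk test on the trial's own data chooses between the mixed ANOVA and a gamma GEE; with this fallback and 10 runners per arm, the two-stage rule can run at about 9–12% error instead of 5%

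*Protocol article*

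**What the plan says.** All references are to the protocol article.

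- **Data analysis** announces the check: "Data normality and sphericity will be tested using the Shapiro-Wilk" test, with Mauchly's test for sphericity. It then names two main models for the outcomes: "a repeated measures ANOVA with a 3-by-3 mixed-model (parametric data) or the Generalized Estimation Equations procedure with gamma distribution model (non-parametric data". The parametric and non-parametric labels are the only criterion separating them. The section also states: "Significance level of p <0.05 will be adopted".
- **Sample size** rests on one of the two models: "we used ANOVA: repeated measures, within-between interaction", giving 21 participants, raised to 30 for losses.
- **Data collection** describes the pain measure: "which consists of a numerical scale from 0 to 10 points, where 0 means no pain". The recording step (whole points, half points or finer) is not given.
- **Participants** sets an entry level for pain during running: "with intensity of at least 3/10 on the Visual Analogue Scale (VAS".

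The abstract and the Outcomes measures section name different pain scores as primary. Both use the same 0–10 scale, so the point applies either way.

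**The concern.** The switch is not written as an explicit if-then, but the text offers no other way to decide whether data are parametric. The rule itself is fixed in advance. What is not fixed is which test will deliver the result, because that depends on a preliminary test of the outcome data.

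Three things are at stake. First, the error rate that matters is that of the whole two-stage procedure, and it need not equal the 5% the protocol adopts. Secondly, the stated 99% power describes the ANOVA interaction test and not the GEE. Thirdly, the branches may estimate different quantities: differences in means under the ANOVA, ratios of means under a gamma GEE if a log link is used.

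**Working it through.** **1. The plan's own figure.** From the Sample size section, partial eta squared is 0.19, so f = √(0.19/0.81) = 0.484 (stated as 0.48). For N = 21, 3 groups and 3 measurements, with a correlation between measurements of 0.5 and epsilon of 1 (both assumed, not stated):

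- noncentrality = f² × N × m / (1 − ρ) = 0.2346 × 21 × 3 / 0.5 = 29.6
- degrees of freedom = (3 − 1)(3 − 1) = 4 and (21 − 3)(3 − 1) = 36
- power = 0.990

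The stated 21 is reproduced, and it belongs to the ANOVA branch.

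**2. Switching by chance alone.** The level of the Shapiro-Wilk test is not stated; 0.05 is assumed. For exactly normal data and independent tests:

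- three visits, arms pooled: 1 − 0.95³ = 0.143
- nine group-by-visit cells: 1 − 0.95⁹ = 0.370

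These two figures need no assumption about the pain scale.

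**3. Switching for 0–10 pain scores.** Simulation with 10 per arm, no treatment effect and three pooled visit tests. The SD and the recording step are assumptions, so a range is shown:

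- whole points, SD 1.5: about 80%
- whole points, SD 2: about 45%
- half points, SD 1.5: about 25%
- 0.1 steps, SD 1.5: about 12–14%, which is the chance level

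Whole-point scores fail the test because of ties, yet the ANOVA interaction test on whole-point data had simulated error between 4.9% and 5.7%. The test therefore often discards a valid model.

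**4. Error of the fallback.** A gamma GEE with log link, exchangeable working correlation and robust Wald test (link, correlation and test assumed) had null error of about 13–16% with 10 per arm, say 14%. Robust Wald tests are known to be liberal with so few clusters.

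**5. Error of the rule as written.** The simulated two-stage error for whole-point pain is about 11–12% at SD 1.5 and 9% at SD 2. A rough mixture, treating the switch as unrelated to the two test results, explains this:

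- SD 1.5: 0.80 × 0.14 + 0.20 × 0.05 = 0.122
- SD 2: 0.45 × 0.14 + 0.55 × 0.05 = 0.091

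If the GEE error stays near 14%, the same approximation (not simulated) gives less for finer recording:

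- half points: 0.25 × 0.14 + 0.75 × 0.05 = 0.073
- 0.1 steps: 0.13 × 0.14 + 0.87 × 0.05 = 0.062

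A separate set-up, with correlation 0.5 and zero scores dropped because a gamma model cannot take them, gave 13–15% for whole points at SD 1.5.

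**6. Disagreement between branches.** For whole-point pain at SD 1.5, the ANOVA and the GEE reach opposite verdicts at 5% in about 10% of trials with no effect and about 25% at a 0.7 SD effect. With a large effect they almost never disagree.

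**The case against.** **The rule is prespecified and the analyst is blinded to group.** Both are true, and they limit deliberate choice of the more favourable model. They do not restore the 5% level: the inflation arises when the rule is followed faithfully.

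**The harm belongs to the fallback, not to the switch.** This largely stands. With the same switch but a rank-transform ANOVA as fallback, the two-stage error was 5.7%, equal to that of the ANOVA alone. The branches then disagreed in only 2.7% of null trials and 8.7% at 0.7 SD. A reader might infer that any data-driven choice of model would inflate error to this degree; the evidence does not support that. The point concerns this switch with this fallback.

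**The treatment effect does not trigger the switch.** This also stands. A reader might infer that an effective program, by making pooled scores two-humped, would itself push the analysis into the GEE. With continuous data and pooled visit tests, switching was 13.8% at no effect, 14.2% at 0.7 SD, 13.9% at 1.2 SD and 14.7% at 1.6 SD. It rose only at 2 SD (18%) and 2.5 SD (28%).

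**The high switch rate depends on unstated inputs.** This is correct. The 80% needs whole-point scores and SD 1.5, so the documents do not show that pain would usually go to the GEE. The article speaks of data normality but does not exclude testing residuals. With whole-point scores, testing residuals centred within cells lowers switching to 34%, 19% and 13% at SD 1.5, 2 and 2.5.

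**Detail may sit elsewhere.** What follows from Mauchly's test, and the unit to which Shapiro-Wilk is applied, are details that a condensed article may leave to a fuller plan, so their absence is not counted here. The two-model rule is different, because the article states it.

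**Conclusion.** The point holds in limited form. As written, a Shapiro-Wilk result selects the main model outcome by outcome, and one of the two candidates does not hold its level at this sample size. For pain in whole points with SD 1.5–2 and 10 per arm, the procedure has about 9–12% error where the protocol adopts 5%, although the ANOVA alone would hold about 5%. With finely recorded scores, switching falls to the chance rate and the inflation becomes small.

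The size rests on assumptions that the documents do not supply: recording step, SD, correlations between visits, a Shapiro-Wilk level of 0.05, and a log link with robust Wald test for the GEE. The rounding part concerns the two pain scores, and much less the 0–100 function scale or the angles.

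A reader might also multiply the chance rates over all nine outcomes and conclude that at least one switch is nearly certain. That would require independent outcomes, which measurements on the same runners are not.

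**What to change.** Delete the normality switch from the Data analysis section and name one main model in advance for every outcome. The natural choice is the repeated measures ANOVA already used for the sample size, with the Greenhouse-Geisser correction applied; an equivalent linear mixed model would also serve. State that residuals will be examined descriptively and that this will not change the main model. Any alternative, including a GEE, can stay as a labelled sensitivity analysis.

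The cost is one paragraph of wording, agreed before outcome data are seen. No new data are needed, and the main analysis then matches the model behind the sample size.

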## Methods

### Study design

This will be a randomized, single-blind, parallel group, three-arm superiority clinical trial, using a 1:1:1 allocation rate and six-month follow-up. The three arms of the study will be composed of three groups: a group that will perform partially supervised gait retraining with a focus on impact (group A), a group that will perform partially supervised gait retraining focusing on cadence (group B), and a control group that will not perform any intervention (group C). The study outcomes will be evaluated before (t0), immediately after (t2), and six months (t24) after starting the protocol. The study will be carried out at the Instituto Trata located in the city of Goiânia, Goiás, Brazil. This protocol was written in accordance with the SPIRIT (Standard Protocol Items: Recommendations for Intervention Trials) (S1 and S5 Files) and the results will be reported in accordance with the CONSORT (Consolidated Standards Of Reporting Trials). Information regarding the dissemination of the results can be found in S2 File.

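### For parametric outcomes, the planned repeated measures ANOVA keeps only participants with all three visits; this contradicts the intention-to-treat promise and affects the two-week comparison

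*Protocol article*

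**What the plan says.** All references are to the Protocol article.

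- **Data analysis, method.** In SPSS, parametric outcomes get "a repeated measures ANOVA with a 3-by-3 mixed-model (parametric data"), with time (t0, t2, t24) as the repeated factor and group as the between-person factor. Sphericity is checked with Mauchly's test. Outcomes judged non-parametric go to generalized estimating equations (GEE) with a gamma distribution.
- **Data analysis, population.** "Intention-to-treat analyses will be conducted where the subjects will be analyzed independently of adherence to the protocol or retention in the follow-up".
- **Rehabilitation programs.** If persistent pain makes participation impossible, the runner counts as a drop-out because of injury, and the data gathered up to then are to enter the analysis.
- **Outcomes measures.** At withdrawal, pain and function are collected where this can be done. Kinematics are not mentioned there.
- **Sample size.** "The total sample size obtained was 21 participants", and "to account for losses during the follow-up period, the final sample size will be 30 participants".
- **Introduction.** The comparison of the two-week programs with control is the primary objective. The six-month comparison is secondary.

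**The concern.** A 3-by-3 mixed-design ANOVA works on one row per person with three filled cells. A row with a gap is dropped whole. A runner measured at t0 and t2 who misses t24 therefore leaves the t0-to-t2 comparison as well, although both values are on file. The method named and the population promised in the same section cannot both hold once anyone is lost.

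Two things are at stake. Valid t2 data are discarded because of something that happens months later. And those who remain may be a selected group: controls get no retraining or guidance for 24 weeks, the monthly calls ask about treatment sought elsewhere, and persistent pain is itself a defined route to drop-out. If such losses fall unevenly on the arms, the two-week contrast shifts along with the six-month one.

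**Working it through.** **1. The plan's own sample size.** Inputs from Sample size: partial eta squared 0.19, "effect size f = 0.48 (obtained through eta-partial square value"), "level of confidence = 0.05", power 99%, "number of groups = 3; number of measurements = 3".

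- f = √(0.19 / 0.81) = 0.484, which agrees with 0.48.
- Noncentral F for the within-between interaction: λ = f²·N·m / (1 − ρ), df1 = (3 − 1)(3 − 1) = 4, df2 = (N − 3)(3 − 1).
- The correlation ρ and the sphericity correction are not stated. Assuming ρ = 0.5 and ε = 1, N = 21 gives λ = 0.2304 × 21 × 3 / 0.5 = 29.03, df2 = 36 and power 0.9904. N = 18 gives 0.973. The stated 21 is reproduced.
- Range at f = 0.48, in multiples of 3: ρ = 0 needs 42, ρ = 0.3 needs 30, ρ = 0.5 needs 21, ρ = 0.7 needs 15.

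**2. Room for losses.** 30 − 21 = 9, and 9/30 = 30%. With "using a 1:1:1 allocation rate and six-month follow-up", that is 10 per arm at randomisation and, if losses are even, 7 per arm with complete rows.

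**3. Precision lost at t2.** Suppose all losses occur after t2 and are even across arms. Using all available data, a two-arm t2 contrast rests on 10 per arm; under the ANOVA it rests on n complete rows per arm. For a common SD the standard error is proportional to √(2/n), so the ratio is √(10/n) whatever the SD:

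| Lost in total | Complete rows per arm | Standard error ratio |
|---|---|---|
| 3 | 9 | √(10/9) = 1.05 |
| 6 | 8 | √(10/8) = 1.12 |
| 9 | 7 | √(10/7) = 1.20 |

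**4. Possible bias at t2.** If a fraction d of an arm is lost and those people's mean pain is δ points above that of the arm's completers, the completer mean is d·δ too low. With d = 0.3, assumed δ of 1, 2 or 3 points gives 0.3, 0.6 or 0.9 points. This is the error in one arm's mean. The error in a contrast is the difference between the two arms' values of d·δ: zero if both arms lose the same kind of people at the same rate, and the full amount if only one arm does.

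A simulation illustrates the unequal case. Assumptions: 10 per arm, SD 1, within-person correlation 0.5, a true t2 effect of −1.0 in both retraining arms, nine people lost, loss more likely with higher t2 pain, and about 20,000 trials. One rule governs loss in every arm, but controls have more pain at t2 and so are lost more often. The t0-to-t2 contrast of one retraining arm with control averages −1.00 with all 30 and −0.82 in completers. Its empirical SD rises from 0.45 to 0.56.

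**5. The other branch.** GEE uses whatever values a person has. Whether a drop-out counts would therefore depend, outcome by outcome, on the normality assessment.

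**The case against.** The best counter-argument is that the plan nowhere says incomplete participants are excluded. It states the opposite aim, and an ANOVA run on imputed data would meet it; how gaps are filled is commonly left to an analysis plan that is not shown. This would answer a complaint that missing-data handling is absent. It does not answer this point, because the article names a method that needs complete rows, promises a population that includes incomplete ones, and gives nothing that joins the two.

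The term mixed-model could also be read as a linear mixed model. However, the 3-by-3 layout, the repeated measures ANOVA label, Mauchly's test and the within-between ANOVA used for sample size all point to the classical design. If a linear mixed model is meant, the wording still needs correcting.

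Several limits do stand:

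- The conflict is confined to the ANOVA branch. Bounded 0–10 pain scores may go to GEE, in which case the deletion would not touch them.
- Collecting pain and function at withdrawal may reduce gaps in those outcomes. It does nothing for kinematics, and a value taken at withdrawal is not a t24 value.
- A reader might infer that the plan expects to lose 30%. It gives no dropout rate; 30% is only the room between 21 and 30.
- A reader might infer that the trial becomes underpowered. The sample size was set for 21 analysed, so this loss does not undo the stated 99%.
- A reader might take 0.6 points as the bias in the treatment effect. It is the error in one arm's mean under an assumed δ, and the documents do not show that loss will differ by arm.

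**Conclusion.** The point holds for the parametric branch. The stated ANOVA cannot deliver the intention-to-treat analysis promised in the same section, nor the promised use of an injury drop-out's earlier data. The conflict reaches the primary two-week comparison because one model covers all three visits.

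At most 9 of 30 (30%) would be excluded within the plan's own margin. If those losses all come after t2 and are even across arms, the standard error of a two-arm t2 contrast is about 1.20 times that from all available data; with fewer losses it is between 1.00 and 1.20 times. Bias in the contrast is possible, but its size is unknown and it requires pain-related loss that differs by arm. The harm is the broken population promise, avoidable loss of precision and possible selection bias. It is not a failed sample size, and it does not make every planned analysis a completers analysis.

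**What to change.** - Replace the repeated measures ANOVA with a likelihood-based linear mixed model (SPSS MIXED, REML, unstructured covariance) with t0, t2 and t24 all as outcomes and terms for group, visit and group-by-visit, preferably with a common baseline mean across arms. Keep t0 as an outcome: a model with t0 as covariate and only t2 and t24 as outcomes would omit anyone lost before t2. With t0 as an outcome, such a person still contributes the baseline value, though little information on the treatment effect.
- Drop Mauchly's test, which this model does not need.
- State that the analysis assumes data are missing at random.
- Apply the same all-randomised population in the GEE branch, and note that unweighted GEE generally needs the stricter assumption of data missing completely at random.
- Report completers only as a sensitivity analysis.

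Multiple imputation over all 30 would also remove the contradiction, if the plan says so. The cost is a change of wording before analysis, in software already named, with no effect on recruitment or visits. The downsides are small: reliance on missing at random, which the data cannot prove, and slightly more analysis work.
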